#### Physical function

Mobility will be assessed in the ICU on days 1, 6 and 11 of study enrolment (or at ICU discharge, whichever is earlier) and at hospital discharge, using the ICU Mobility Scale, a validated measure with excellent clinometric properties [104, 105]. In addition, functional assessment (‘timed up and go’ and ‘sit to stand’) will be performed at hospital discharge. ‘Timed up and go’ will involve measuring the time taken to stand up from a standard chair, walk a 3-m distance at normal pace and return to the chair; for ‘sit to stand’, the number of times that the participant is able to completely stand upright from a standard chair and sit back down fully within 30 s will be assessed. Due to the study population being frail, use of aids will be permitted and documented.

#### Clinical outcomes

Clinical outcomes between participants in the intervention and control arms will be compared: incidence and duration of delirium; incidence, duration and severity of acute kidney injury (assessed using the AKIN classification) [106]; duration of specific organ support (mechanical ventilation, renal replacement therapy, mechanical or pharmacological cardiovascular support); days alive and without a ventilator in the first 28 days of hospital stay; length of ICU and hospital stay; and hospital and 3-month mortality.

#### Laboratory assessment

A 10-ml urine sample (collected from an indwelling urinary catheter) and 1 × 10 ml EDTA, 3 × 4 ml EDTA, 1 × 4 ml serum, 1 × 3 ml Tempus™ RNA blood tube samples will be collected on days 1, 6 and 11 of study enrolment from indwelling arterial cannulae, and via venepuncture at hospital discharge. In addition, 1 × 4 ml EDTA blood samples will be taken at 3 and 24 h after the first RVOS session in patients randomised to the intervention arm and similarly at 3 and 24 h after baseline assessment in control participants. Plasma and serum will be separated from the EDTA and serum tubes, and the urine sample and Tempus™ blood RNA will be stored at − 80 °C. The, 1 × 10 ml EDTA will be processed to isolate peripheral blood mononuclear cells (PBMCs) using the Optiprep™ protocol [107], which will be stored at − 80 °C until analysis.

Samples will be stored in accordance with the Human Tissue Act (2004) beyond the end of the trial to allow for various laboratory analyses to evaluate mechanisms behind the effect of RVOS. Biomarkers that will be analysed are presented in Table 4. Further biomarkers may be studied to evaluate mechanisms of effect as scientific evidence dictates.

**Table 4 Tab4:** Laboratory analysis

Sample	Biomarkers
Plasma and serum	Muscle anabolic marker insulin-like growth factor 1 Muscle catabolic marker Myostatin Inflammatory cytokines interleukin (IL)-6, IL-10, tumour necrosis factor α, granulocyte–macrophage colony-stimulating factor, macrophage inflammatory protein 1, transforming growth factor β1 Angiogenic factors vascular endothelial growth factor, hypoxia inducible factor 1α
Tempus RNA tube	MicroRNAs linked with muscle atrophy such as miR-29b, miR-542-5p and miR-424-5p [108]
Peripheral blood mononuclear cells	DNA damage/repair enzymes GAD45a and APE-1
Urine	Oxidative stress-derived DNA damage marker 8-hydroxy deoxyguanosine

### Statistical analysis

The statistical analysis addresses the objectives of demonstrating the safety and tolerability of applying RVOS to the lower proximal limb of ICU patients, and assessing the feasibility of undertaking a larger-scale study to demonstrate efficacy. As a feasibility trial, the statistical analysis will primarily be exploratory in nature, and thus hypothesis generating rather than confirmatory.

The primary objective of safety will be evaluated based on the frequencies and percentages of adverse events categorised by severity, group and site. The tolerability will be evaluated by assessing VAS pain scores of the intervention arm at each time point in terms of means and standard deviations.

The main feasibility outcome of recruitment will be evaluated as the percentage of randomised participants out of total eligible patients. The number of participants randomised as a percentage of targeted recruitment will also be computed. If data are available, the average number of research assistants’ hours spent on recruiting one participant will also be computed. Retention will be evaluated as the proportion of participants remaining at each time point compared to the number recruited in each arm.

Descriptive statistics will be used to summarise all response variables by site, time point and treatment group. Means and standard deviations will be computed for continuous outcomes and frequencies and percentages will be computed for categorical/dichotomous outcomes. The relationship with potential confounding factors—such as site, demographic data, delirium during ICU stay, severity of illness, length of ICU stay, sepsis (defined using SOFA score), and use of drug treatment (such as corticosteroids, neuromuscular blocking drugs, statins and propofol)—will be explored.

The following inferential statistics will be performed strictly for the purpose of identifying the directions and magnitudes of effects rather than to evaluate the statistical significance of the results due to inadequacy of statistical power.

Outcome measures recorded at a time point (such as ‘timed up and go’ and ‘sit to stand’ assessment) and clinical outcomes (such as duration of mechanical ventilation and length of ICU and hospital stay) will be compared between the two arms using an independent-sample *t* test.

Repeated outcome measures such as the RFCSA and echogenicity, superficial femoral artery measures (resting diameter and blood flow, FMD and reactive hyperaemic response), ICU mobility score, MRC-SS and handgrip strength data will be analysed separately as the response variable in a general linear mixed model using SAS PROC MIXED, with group (the dichotomy of standard care or RVOS), site, baseline measure, time and group × time interaction as fixed effects and subject as random effects. Appropriately selected covariates will be included in the model as fixed effects to adjust for the variability caused by these covariates.

All statistical analyses will be performed by the Trial Statistician at Surrey Clinical Trials Unit (CTU) according to a pre-specified Statistical Analysis Plan, which will be finalised and signed off before the database lock.

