## Methods

### Primary objectives

The primary objective of the trial is to determine whether it is safe and tolerable to apply RVOS to a proximal lower limb of ICU patients.

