### Recruitment and randomisation process

All sequential ICU admissions will be screened for eligibility. Eligible patients with mental capacity for informed consent will be approached, the risks and benefits of participation explained and written informed consent will be obtained before enrolment by the investigator physician. However, we envision that the majority of eligible patients will be receiving invasive mechanical ventilation and requiring sedation, and thus lacking capacity to consent. In this instance, declaration of agreement will be sought from the patient’s ‘Personal Consultee’ who may be a representative, partner or close friend. Once the participant recovers and is capable of understanding the details of the trial, they will be approached to provide their informed consent retrospectively. If the patient chooses to withdraw from the trial, they will be given the choice of having their existing data and samples destroyed or excluded from final analysis.

Upon informed consent or declaration of agreement, eligible patients will be randomised to either the intervention arm or the control arm in a 1:1 ratio. Separate randomisation lists have been prepared for each site by an independent statistician and uploaded to the study electronic data capture system PROMASYS (Surrey Clinical Trials Unit). In addition, the randomisation list and corresponding envelopes containing randomisation assignments will be stored in the trial file. Randomisation, outcome measure assessments and RVOS intervention will be performed by a research assistant unblinded to patient allocation.

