**Fig. 3 Fig3:**
[figure not shown]
Protocol for repetitive vascular occlusive stimulus (RVOS). Each session of RVOS includes four repetitions of 5-min inflation of pneumatic cuff to 50 mmHg supra-systolic blood pressure (SBP) followed by 5 min of complete (0 mmHg) cuff deflation

Vital signs such as blood pressure, heart rate and the saturation of peripheral arterial blood with oxygen will be monitored before and during RVOS, and the session will be terminated if the defined criteria are met (Table 2).

**Table 2 Tab2:** Termination criteria for repetitive vascular occlusion stimulus (RVOS) session

1. Heart rate < 40 bpm or > 180 bpm 2. Systolic blood pressure < 80 mmHg or > 200 mmHg 3. Mean arterial blood pressure < 60 mmHg or > 120 mmHg 4. Peripheral capillary oxygen saturation (SpO_2_) < 88% 5. Pain score > 8/10 on visual analogue scale and unwillingness to proceed with RVOS intervention 6. Objective signs of tissue injury felt due to cuff inflation	

A clinical bedside nurse will be present throughout the RVOS session and will monitor facial expression, limb movement and ventilation compliance for any sign of distress in the sedated participants. In the event that the patient experiences significant discomfort, the cuff pressure will be lowered to a pressure that is tolerated by the participant, and such adjustments will be recorded. If conscious, tolerability of the intervention will be evaluated by asking the participant to rate the pain of the procedure on a visual analogue scale (VAS). After each session, the intervention leg will be examined for signs of arterial insufficiency or tissue injury. In addition, serum creatinine kinase levels will be monitored daily as an indicator of muscle damage.

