#### Tolerability

The VAS pain score will be used to assess the tolerability of RVOS.

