## Discussion

This study will be the first to assess the safety, tolerability, feasibility and acceptability of RVOS in ICU patients. The effect of RVOS on muscle mass atrophy and weakness, and on arterial dysfunction observed in ICU patients, will also be explored.

Thirty-two ventilated critically ill patients with at least two other organ failures will be recruited to the study. Multiple organ failure patients were chosen as the study population because these patients undergo more pronounced muscle wasting (16% decrease in the RFCSA compared to 3% in single organ failure patients within 7 days of ICU admission) [21].

RVOS will be performed using equipment conventionally and safely used for vascular disease diagnostics and routinely used during vascular and orthopaedic operations. Control participants will receive standard care and no sham treatment (repeated cuff inflation at lower pressure) so as to avoid any detrimental impacts of isolated venous occlusion. Participants will thus not be blinded in the study. However, this is unlikely to introduce bias to the objective measures as muscle and arterial ultrasound images will be anonymised and analysed blinded to subject identity, study time points and group allocation.

The tolerability of RVOS cannot be assessed when participants are ventilated and sedated. Even when participants are extubated and off sedation, delirium (an acute brain dysfunction) is common in critically ill patients and can influence the VAS score. CAM-ICU assessment will be performed and the mental state of the participant during the RVOS session will be recorded to observe any effects of delirium on the VAS score.

Ultrasound assessments of muscle mass and quality and arterial function can be performed when participants are sedated; however, muscle strength and physical function measures are volitional assessments and require the participant’s full attention and cooperation. Therefore, sedation, lack of willingness to participate or lack of mental capacity due to delirium can prevent these outcome assessments. These measures will therefore only be performed when the participant is off sedation and CAM-ICU negative; this could lead to the time points when the strength and physical function assessments are performed varying between participants.

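### Tolerability is judged on mean VAS alone, which mixes full-pressure and reduced-pressure sessions and leaves out the recorded pressure reductions and pain-related stops

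*Protocol article*

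**What the plan says.** Under Primary objectives the article states: "The primary objective of the trial is to determine whether it is safe and tolerable to apply RVOS" to a proximal lower limb. Under Primary outcome measures, the tolerability entry is one sentence: "The VAS pain score will be used to assess the tolerability of RVOS". The Statistical analysis section completes the definition: "tolerability will be evaluated by assessing VAS pain scores of the intervention arm at each time point in terms of means" and standard deviations. It attaches no proportion, threshold or count of intolerant sessions.

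The section on the RVOS intervention says who is scored: "If conscious, tolerability of the intervention will be evaluated by asking the participant to rate the pain of the procedure". The Discussion concedes the gap this leaves: "The tolerability of RVOS cannot be assessed when participants are ventilated and sedated". For significant discomfort, the intervention section says that "the cuff pressure will be lowered to a pressure that is tolerated by the participant, and such adjustments will be recorded". Table 2 ends a session for, among other reasons, a pain score above "8/10 on visual analogue scale and unwillingness to proceed with RVOS intervention".

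For a patient who chooses to withdraw, Recruitment and randomisation process says "they will be given the choice of having their existing data and samples destroyed or excluded from final analysis".

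**The concern.** A pressure reduction for discomfort is itself evidence about tolerability, and so is a session stopped for pain. The article collects both but summarises tolerability with a statistic that uses neither. Once the pressure is lowered, the participant is rating a weaker stimulus, possibly no longer the complete arterial occlusion that the intervention section describes. That score is nevertheless averaged with full-pressure scores.

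The article makes safety, feasibility and acceptability the conditions for designing a larger trial. A low mean VAS could be read as showing that RVOS as specified is well tolerated, when some of the scores belong to a reduced version of it.

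**Working it through.** **Plan's own figure.** The article states no figure for tolerability. Its one precision statement, ±15.9 points around 30%, concerns failure to deliver RVOS. It reproduces as 1.96 × √(0.3 × 0.7 / 32) = 0.159 and is not used below.

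**Step 1. Where each event goes under the text as written.**

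| Event | In the tolerability summary? | Elsewhere? |
|---|---|---|
| Conscious, completed at set pressure | Yes, as VAS | Counts as delivered |
| Conscious, pressure lowered | VAS enters, not separated; timing not stated | Reduction recorded, no named output |
| Conscious, stopped for pain | The score above 8 enters if recorded; the stop does not | No named output by reason |
| Sedated, with or without distress | No score | Pressure changes recorded, no named output |
| Participant withdraws from the trial | Scores removed | Retention by arm and time point, no reasons |

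**Step 2. Effect of VAS timing (all inputs assumed).** Let a share r of conscious sessions score 8 at the set pressure and 4 after lowering, and let the rest average 3.

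- VAS before lowering: (1 − r) × 3 + r × 8 = 3 + 5r
- VAS after lowering: (1 − r) × 3 + r × 4 = 3 + r
- Gap: 4r

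| r | Before | After | Gap |
|---|---|---|---|
| 10% | 3.5 | 3.1 | 0.4 |
| 20% | 4.0 | 3.2 | 0.8 |
| 30% | 4.5 | 3.3 | 1.2 |

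If VAS is taken after lowering, tripling the share of weakened sessions moves the mean by 0.2. If it is taken before, the mean is not pulled down, but a mean of 4.0 still does not tell the reader that r is 20%.

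**Step 3. A second assumption.** The Background cites a VAS of 3.6 ± 3.4 in another population. Take a beta distribution on 0–10 with that mean and SD (the shape is assumed). Replacing every score above 8 by 8 affects 17% of scores and gives a mean of 3.4. Replacing every score above 5 by 5 affects 34% and gives 2.6. The direction is the same as in Step 2, with a shift of 0.2 to 1.0.

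**Step 4. Precision with conscious raters only.** Half-width = t(0.975, n − 1) × 3.4 / √n, with one score per participant.

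- n = 16: 2.131 × 3.4 / 4 = ±1.8
- n = 8: 2.365 × 3.4 / 2.828 = ±2.8
- n = 4: 3.182 × 3.4 / 2 = ±5.4

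**Step 5. Does the delivery criterion fill the gap?** A full course is 1 + 2 × 9 = 19 sessions, so 16 participants staying throughout have 16 × 19 = 304. Table 3 asks for 80%, and 0.8 × 304 = 243.2. So 244 delivered sessions meet the criterion with 60 missed, for whatever reason. Table 3 does not say whether a reduced or interrupted session counts as performed. If it does, the criterion puts no limit on reductions.

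**The case against.** The strongest reply is that the trial is openly exploratory, that the Discussion admits the sedation and delirium limits, and that other outputs would expose poor tolerance. Table 3 tracks session delivery, the Statistical analysis section reports retention by arm, and participants, consultees and staff are interviewed on acceptability. The unseen SAP may also list pressure changes and denominators. Much of this stands: missed sessions and drop-out would be partly visible. But those outputs are not split by reason, none separates reduced-pressure sessions, and the article itself fixes the primary measure as mean VAS.

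Some stronger readings are tempting but not supported:

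- A reader might infer that pain-related stops lower the mean. The pain criterion in Table 2 requires a score above 8, so such a score, if recorded, raises it.
- A reader might infer that VAS exists only for a later, awake subset. Table 1 admits CPAP patients and the article provides for patients with capacity to consent, so some could score from the first session.
- A reader might infer that lowering the cuff must reduce the recorded score. The article does not say when VAS is taken, and a rating of the procedure could cover the whole session.
- A reader might infer that withdrawal removes intolerant patients. The clause covers any reason and both arms, and does not mention pain. What stands is that anyone who withdraws leaves the average under either option, so the number needs to be reported.
- A reader might infer strong skew from 3.6 ± 3.4. A mean and SD do not fix the shape.

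**Conclusion.** The point holds in a limited form. As written, the primary tolerability measure can mix scores from set and reduced pressures, comes only from conscious participants, and is silent on the share of sessions weakened or stopped for pain. It can look acceptable whatever that share is.

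The numerical bias in the mean is not known. Under the assumptions in Step 2 it runs from none (VAS taken before lowering) to 0.4–1.2 points (VAS taken after, with 10–30% of conscious sessions affected). A shift of that size is smaller than the sampling uncertainty of ±1.8 with 16 raters. The main loss is therefore the missing proportion, more than the shift in the mean. This is worth correcting because tolerability is half of the primary objective and most of the data needed are already collected.

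**What to change.** In the SAP, before database lock:

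- Beside VAS, report for each RVOS participant the percentage of started sessions completed at the set pressure with no reduction or termination for pain or observed distress. Give a 95% CI that respects clustering by patient, for example one based on patient-level percentages.
- Show conscious and sedated sessions separately. Sedated patients cannot report pain, so pooling them would count their sessions as tolerated largely by default.
- Report VAS with the number assessable out of sessions given and the percentage above 8/10. Show scores from reduced-pressure sessions and from CAM-ICU-positive sessions separately, and state when VAS was taken relative to any reduction.
- Report withdrawals by arm, including those whose data were destroyed or excluded, with reasons where known.

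Cuff pressure and VAS per session, pressure adjustments and mental state during sessions are already recorded. The article does not say that the reason for a stop, or the nurse's observation of distress, is recorded; where it was not, say so. The cost is slightly more analysis, and tolerability may look less favourable. Recruitment closed in February 2019, so a change to the consent form would come too late for this trial and is not proposed. Nothing here changes the pressure, the termination criteria or any other part of clinical management.

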### Sample size rationale

A total of 30 participants is recommended for pilot and feasibility trials [97]. To allow for balance in the stratification factors (gender and study site), a sample size of 32 participants was chosen, which will allow us to estimate a failure to deliver RVOS in the intervention arm of 30% to within a 95% confidence interval of ± 15.9%.

Based on an anticipated average rate of recruitment of 6 patients/month, 50% screening failure due to weekends, 20% decline of consent and 30% death before trial completion, we aim to recruit 1.6 patients per site per month. Recruiting from two sites, one starting 2 months after the other, is expected to yield 47 patients over 16 months. Recruitment will continue until 32 ICU survivors have been studied (16 patients in each group).

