### Study protocol

Figure 2 illustrates the schedule of study procedures and outcome measure assessments. Briefly, within 24 h of enrolment and randomisation, baseline assessments will be completed. These will include ultrasound assessment of muscle and arterial vascular function; blood and urine sample collection and physical function assessment using the ICU mobility score; recording of clinical characteristics such as medical history, diagnosis and severity of illness (assessed using the Sequential Organ Failure Assessment (SOFA) score); documentation of physical function (assessed using the Katz Index of Independence in Activities of Daily Living score) and nutritional status (assessed using the Malnutrition Screening Tool) prior to illness.

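### Outcomes compared by t test leave out site, although randomisation is by site and the mixed model includes it: the intervals may be somewhat too wide (minor)

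*Protocol article*

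**What the plan says.** All references are to the protocol article.

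- **Statistical analysis, outcomes recorded once and clinical outcomes.** Timed up and go, sit to stand, duration of ventilation and lengths of ICU and hospital stay "will be compared between the two arms using an independent-sample" t test. No site term or covariate is named.
- **Statistical analysis, repeated outcomes.** The mixed model's fixed effects include "site, baseline measure, time and group" by time, and selected covariates may be added.
- **Recruitment and randomisation process.** Patients are "randomised to either the intervention arm or the control arm in a 1:1 ratio", and "Separate randomisation lists have been prepared for each site by an independent statistician". Gender is not mentioned here.
- **Sample size rationale.** "To allow for balance in the stratification factors (gender and study site), a sample size of 32 participants was chosen". Here gender is named as a stratification factor beside site.
- **Study protocol.** SOFA and the pre-illness Katz index are recorded at baseline.
- **Statistical analysis, purpose.** The inferential results are meant to show the direction and size of effects, not significance. Relationships with site, severity of illness and other factors are to be explored.

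**The concern.** When allocation is balanced within site, differences between sites cancel out of the treatment comparison. A two-sample t test does not use this: it leaves the between-site variance in its residual, so the standard error is larger than the design warrants. The two ICUs could plausibly differ in discharge practice, for example, which would bear on length of stay.

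The plan includes site for one family of outcomes and omits it for the other, and gives no reason. What is at stake is the width of the interval around each estimated effect. That matters somewhat here, because the size of effects is the stated purpose of these analyses and the results are to inform a later trial.

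**Working it through.** **Inputs.** From the article: 32 ICU survivors, 16 per arm, 1:1 allocation, two sites. Assumed: the share of outcome variance (R²) explained by site or by a baseline score, since the article gives none; equal sites; exact balance of arms within site; a normally distributed outcome; and 24 patients assessable at hospital discharge as a lower case. The article gives no precision figure for the t-test outcomes, so there is none to reproduce. Its only one, ±15.9% for failure to deliver the intervention, is reproduced with n = 32: 1.96 × √(0.3 × 0.7/32) = 0.159.

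**Step 1: site only, n = 32.** In units of the total variance, the t test's residual mean square is (1 − R²) + R² × 32/30, on 30 degrees of freedom. With site in the model it is 1 − R², on 29. The t quantiles are 2.042 and 2.045, a ratio of 1.0014. The interval ratio, adjusted to unadjusted, is therefore √[(1 − R²)/((1 − R²) + R² × 32/30)] × 1.0014. The simulation used 8,000 replicates per scenario.

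| Site R² | Formula | Simulation | t-test interval too wide by (1/simulated ratio − 1) |
|---|---|---|---|
| 0 | 1.001 | 1.001 | none |
| 0.05 | 0.974 | 0.975 | 2.6% |
| 0.10 | 0.947 | 0.947 | 5.6% |
| 0.20 | 0.890 | 0.887 | 12.7% |

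**Step 2: direction of the error.** In the simulation, the nominal 5% t test rejected a true null in about 4.3% of replicates with a 5% site effect and 2.7% with a 20% site effect. The Monte Carlo standard error near 5% is √(0.05 × 0.95/8000) = 0.24 percentage points. With no site effect the printed value was 4.5%, so only the 20% case stands clearly apart. The direction is conservative.

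**Step 3: optional baseline score.** The approximate standard error ratio against the t test is √[(1 − R²)(1 + k/(n − k − 3))]. Here k is the number of adjusting terms and R² is what they explain jointly. Site plus one score is k = 2; adding gender makes k = 3.

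| R² | k=2, n=32 | k=2, n=24 | k=3, n=32 | k=3, n=24 |
|---|---|---|---|---|
| 0 | 1.036 | 1.051 | 1.056 | 1.080 |
| 0.1 | 0.983 | 0.997 | 1.002 | 1.025 |
| 0.2 | 0.927 | 0.940 | 0.945 | 0.966 |
| 0.3 | 0.867 | 0.880 | 0.884 | 0.904 |

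Setting the ratio to 1 gives the break-even R² = k/(n − 3):

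- k = 2: 2/29 = 0.069 at n = 32 and 2/21 = 0.095 at n = 24.
- k = 3: 3/29 = 0.103 at n = 32 and 3/21 = 0.143 at n = 24.

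The formula treats every term as randomly distributed between arms, so it slightly overstates the cost of a site or gender term that allocation has balanced.

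**The case against.** The best defence is that little depends on these tests. They concern exploratory secondary outcomes in a small pilot whose primary objective is safety and tolerability, and no feasibility criterion in Table 3 rests on them. Under randomisation the unadjusted difference is unbiased, and any error in the interval is on the cautious side. The article also summarises all outcomes by site, plans to explore relationships with site and severity, and defers to a statistical analysis plan. All of this stands, and it limits the severity.

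It does not remove the point. The t test is a method the article states, not a detail it leaves open. The planned exploration is no substitute for adjustment fixed in advance: its list mixes baseline factors with things that happen after randomisation, such as delirium during the stay and length of ICU stay, which is itself a t-test outcome.

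A reader might infer more than the article supports:

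- **That precision is certainly lost, or that adjusting for scores is free.** No R² is given for any of these outcomes. Below the break-even values a baseline score widens the interval.
- **That chance differences in site mix distort the estimate.** This conflicts with the argument about width, which needs the lists to have balanced the arms within site. The article states 1:1 site lists but does not mention blocking, so neither state can be taken as shown.
- **That SOFA goes unused.** Severity of illness is among the factors to be explored.

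**Conclusion.** A minor point of consistency, worth considering. If site predicts outcome and the arms are balanced within site, the t-test intervals are conservative by about 2.6% to 12.7% for an assumed site R² of 5% to 20%. If site predicts nothing, including it costs about 0.1% in width. The case for site therefore does not depend on knowing R². The case for a baseline score does: with site and one score at n = 32, the standard error changes by about +4%, −2%, −7% or −13% at R² of 0, 0.1, 0.2 or 0.3. A reader might infer a risk of false-positive results; the error runs the other way.

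The figures rest on 32 analysed patients with exact balance within site. Deaths may disturb that balance, and the Discussion accepts that deaths after ICU discharge may reduce the data at hospital discharge, where timed up and go and sit to stand are measured.

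**What to change.** In the statistical analysis plan, replace the t test for these outcomes by a linear model with arm and site. Add gender only if it was actually used to stratify: the Sample size rationale names it and the randomisation section does not, so the plan should state which is true. Report the adjusted difference with its 95% confidence interval, and keep the unadjusted difference as a supporting figure.

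Optionally, name one baseline score per outcome in advance: SOFA for durations and lengths of stay, Katz for timed up and go and sit to stand. This pairing is a suggestion, since the article does not show that either score predicts these outcomes.

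The cost is a change of wording before the plan is signed off ahead of database lock, and one to three degrees of freedom: one for site, one for gender if used, one for a score if chosen. No new data are needed.

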#### Muscle strength

On days 6 and 11 and at ICU and hospital discharge, the grip strength of the dominant hand will be assessed using a handgrip dynamometer (Takei Scientific Instruments Co. Ltd, Niigata City, Japan) and manual muscle strength evaluation of the bilateral six upper and lower limb muscle groups (shoulder abductors, elbow flexors, wrist extensors, hip flexors, knee extensors and foot dorsiflexors) performed using the Medical Research Council Sum Score (MRC-SS) [103]. Strength assessments will only be performed if the participant is sufficiently alert and free from delirium.

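### The mixed model for MRC-SS and handgrip strength contains a baseline covariate that the assessment schedule does not supply for these two outcomes

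*Protocol article*

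**What the plan says.** The Statistical analysis section of the protocol article gives one model for all repeated outcomes. After naming rectus femoris area (RFCSA), echogenicity and the superficial femoral artery measures, it continues: "ICU mobility score, MRC-SS and handgrip strength data will be analysed separately as the response variable in a general linear mixed model". The terms, stated once for the whole list, are group plus "site, baseline measure, time and group × time interaction as fixed effects and subject as random effects". A further sentence allows other suitable covariates to be added.

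The Muscle strength section sets the timing: "On days 6 and 11 and at ICU and hospital discharge, the grip strength of the dominant hand will be assessed". MRC-SS follows the same schedule. The section makes testing conditional on the patient being alert enough and not delirious.

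The baseline assessments under Study protocol are ultrasound of muscle and artery, "blood and urine sample collection and physical function assessment using the ICU mobility score", clinical characteristics with SOFA, and pre-illness function (Katz index) and nutrition (Malnutrition Screening Tool). No strength test is named. The same section later puts muscle strength in a collective list of assessments to be repeated on days 6 and 11.

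**The concern.** A model that adjusts for the baseline value needs that value for each patient. For MRC-SS and handgrip, the sections that specify the measurements provide none. PROC MIXED omits any record with a missing covariate, so a covariate missing for everyone leaves nothing to fit.

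The Secondary objectives section says the exploratory results, with strength named among them, should inform the powering of a later trial. The Statistical analysis section says the models are there to show direction and magnitude of effect. For these two outcomes the model cannot do that until it is changed. The change should be written down before the data are seen, because the easiest improvisation, treating the day 6 value as the baseline, adjusts for something measured after treatment has begun.

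**Working it through.** The plan states no figure on this point, so there is none to reproduce. The check compares the schedule with the model terms and then counts usable records.

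**1. Does each modelled outcome have a baseline value?**

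| Outcome in the model | Section giving the timing | Baseline value? |
|---|---|---|
| RFCSA, echogenicity | Muscle mass and quality | Yes |
| Superficial femoral artery measures | Arterial vascular measures (same times as muscle) | Yes |
| ICU mobility score | Physical function; Study protocol | Yes, day 1 |
| MRC-SS | Muscle strength | None listed |
| Handgrip | Muscle strength | None listed |

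The mismatch is confined to the last two rows.

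**2. Is the gap plausible as intended?** Yes. Recruitment and randomisation process expects most eligible patients to be invasively ventilated and sedated. Muscle strength and Discussion restrict strength testing to patients who are alert, no longer sedated and negative on the CAM-ICU. Few could be tested on day 1.

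**3. Usable records (illustration).** Take 32 patients, the target number of ICU survivors, each with all four scheduled strength visits: 32 × 4 = 128 records. Real data would have fewer, but the contrast is the same. With simulated data:

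- baseline term kept, no baseline measured: 0 of 128 records complete, and the fit fails;
- baseline term removed: 128 of 128 used, and the fit converges;
- day 6 relabelled as baseline: 32 × 3 = 96 of 128 remain.

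**4. If a baseline strength test was attempted.** With k of 32 patients testable at baseline, at most 4k records enter the model. If a sedated majority means more than half, and those enrolled resemble those eligible (both assumptions), k is at most 15 and at most 4 × 15 = 60 of 128 records are used. Alertness at baseline precedes treatment, so the arms would still be compared as randomised. But the estimate would describe only the alert minority.

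**5. Is day 6 before treatment?** No. The RVOS intervention section schedules one session on day 1 and two a day on days 2 to 10, for a patient who stays in the ICU throughout. Total: 1 + 9 × 2 = 19. Given by the end of day 5: 1 + 4 × 2 = 9. So 9 of 19 scheduled sessions precede the day 6 measurement.

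**The case against.** **The documents do not prove that no baseline strength test exists.** Study protocol speaks of repeating muscle strength on days 6 and 11, its baseline list need not be exhaustive, the Abstract mentions physical function at baseline, and the schedule in Fig. 2 is not shown. This stands as a limit on certainty. But the sentence about repetition is a collective list, while the baseline list and the Muscle strength section are the specific statements, and the ICU mobility score accounts for physical function at baseline. Step 4 shows that the model is also unsuitable if a test was attempted.

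**A reader might infer that the two strength outcomes have no analysis at all.** They do: the Statistical analysis section promises descriptive summaries of every response by site, time point and group. These need no baseline and are useful inputs for powering a later trial.

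**A reader might infer that a stated share of the treatment effect will be lost by adjusting for day 6.** The documents nowhere propose this. With equal standard deviations, the adjusted day 11 effect would be the day 11 effect minus the within-patient correlation times the day 6 effect. The documents give none of these quantities, so any percentage would only reflect the values assumed.

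**A reader might extend the point to the time factor**, since fixed days are mixed with discharge visits. That is a separate matter of visit coding, commonly left to the SAP. The wording "or at ICU discharge, whichever is earlier" concerns the ICU Mobility Scale, not strength, and the Discussion already accepts that strength assessment times will vary.

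**The consequences are limited.** Safety and tolerability are primary, the analysis is called exploratory, and no feasibility criterion in Table 3 depends on this model. An impossible term would also show itself at the first run. This stands and keeps the severity down.

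**Conclusion.** Wrong as written, for MRC-SS and handgrip only. On the specific text, the stated model has no usable records for these outcomes. On the looser reading it would use only patients alert at baseline, fewer than half under the assumptions in step 4. This is more than missing detail, because the article fixes a covariate that its own schedule does not supply; the permission to add covariates does not remove that one.

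Severity is minor to moderate. The outcomes are secondary and exploratory, and the descriptive summaries stand. RFCSA, echogenicity, the arterial measures and ICU mobility are unaffected. The conclusion rests on the text of Study protocol and Muscle strength, since neither Fig. 2 nor the SAP could be seen; the SAP may already deal with it.

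**What to change.** - For MRC-SS and handgrip only, remove the baseline term from the mixed model.
- If adjustment is wanted, use one or two variables already recorded that treatment cannot have altered, such as baseline SOFA or the pre-illness Katz index. Keep them few: there are about 32 patients, and only those fit for testing contribute strength data.
- State that the day 6 value will not serve as a baseline.
- Keep the baseline term for RFCSA, echogenicity, the arterial measures and ICU mobility.
- Align the sentence in Study protocol about repeated assessments with the Muscle strength and Statistical analysis sections.

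The cost is wording and needs no new data. Trial status reports recruitment complete, so a baseline strength test can no longer be added. The article says the SAP is signed off before database lock, which is the natural place for the change if it is not already there.
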